### Participants

Adults with SCI eligible for the study must have generalized or multifocal spasticity in UE and eventually also in the LE. Their spasticity must be refractory to oral drugs or local treatment [14,15].

In the Netherlands, there are 8 rehabilitation centers with a specialized spinal cord unit. These 8 centers work closely together on patient-related content in the Dutch-Flemish Spinal Cord Society. According to guidelines in the Netherlands, all persons with SCI in the chronic phase are seen by a rehabilitation physician [16-18]. The rehabilitation physician involved in the chronic phase is familiar with the Cervit-B study. In case of generalized therapy-resistant spasticity of the UE and eventually also the LE, patients are referred to RCR by their rehabilitation physician. In RCR, they are seen by the principal investigator ([name]) for assessment to check the indication for cervical administration of ITB. Spasticity is assessed using the Perceived Resistance to Passive Movement (PRPM) and the Modified Ashworth Scale (MAS) [19,20].

When there is an indication for cervical administration of ITB, participants will be informed about the study. When participants are interested, an information letter is given to them. After 1 week, the principal investigator ([name]) will contact the participants to determine their interest in participating in the study and to answer possible questions. If interested in participating, a physical appointment with the principal investigator ([name]) is scheduled to obtain informed consent and to complete the screening procedure to check if it is safe to start phase 1. If it is safe, participants will be seen by the skilled functional neurosurgeon at the outpatient clinic in MST before the start of phase 1. The neurosurgeon will check for operative exclusion criteria and will answer questions. The same neurosurgeon will be involved in the study during all surgical procedures and admission at MST.

The inclusion and exclusion criteria for the Cervit-B study are described in Textbox 1 [21-23].

Inclusion and exclusion criteria.
**Inclusion criteria**
Aged >18 yearsSpinal cord injury (SCI) with a neurological level at or above Th1>1 year after the onset of SCIAn American Spinal Injury Association Impairment Scale of A to D, according to the International Standards for Neurological Classification of Spinal Cord Injury [21]Generalized or multifocal spasticity in UE, and eventually also in LE, refractory to oral drugs or local treatmentProviding written informed consent
**Exclusion criteria**
PregnancyWomen of childbearing potentialWomen who are currently breastfeedingBaclofen allergyUse of oral anticoagulantsIndividuals with active depression, schizophrenia, or bipolar disorders who are still under treatment by a psychiatrist, as exacerbations of these conditions during the use of baclofen have been observed [22]Excessive alcohol use according to the Diagnostic and Statistical Manual of Mental Disorders, Fifth Edition [23], because interactions with alcohol are unpredictable [22]Progressive disease as the cause of SCIConcomitant presence of a terminal disease, such as cancerMuscle or nerve blocks carried out in the last 6 monthsDependent on invasive or noninvasive ventilation other than a Continuous Positive Airway Pressure deviceP_c_CO_2_ (partial pressure of CO_2_ in capillary blood sample)>6.5 kPa or <4.5 kPaNot adequately treated sleep apnea syndrome with an Apnea-Hypopnea Index (AHI) >5. The AHI represents the average number of apneas and hypopneas each hour during sleep.

### Sample Size

No sample size calculation was performed for this pilot safety study. On the basis of a previous comparable study by Bensmail et al [3] with 11 participants, we decided to include the same number of participants. We expect that we need to screen and recruit 25 participants to retain 11 participants at the start of the phase 1 because of the safety criteria for inclusion (Figure 1).

**Figure 1 figure1:**
[figure not shown]
Flowchart of the study phases, including settings, sample size, and parameters to be assessed. ITB: intrathecal baclofen; MST: Medisch Spectrum Twente; RCR: Roessingh Center for Rehabilitation; SCI: spinal cord injury.

### Study Procedures

#### Screening and Recruitment

Before participants are included in the study, they will be assessed by an experienced SCI rehabilitation physician to check the indication for treatment of their spasticity by ITB. If there is an indication, participants will be screened for the presence of SAS by the use of OSAsense (OSAsense BV) [24]. The OSAsense consists of a validated online questionnaire and a nightly saturation and pulse rate measurement (pulse oximetry). The OSAsense algorithm, based on the questionnaire and pulse oximetry, is able to detect SAS with a sensitivity of 100%, a specificity of 35%, a negative predictive value of 100%, and a positive predictive value of 79.4% [25]. If, according to the algorithm, there is any suspicion of SAS, polysomnography will be performed, and the patient will be set up for SAS treatment if necessary. In addition, a morning capillary blood gas sample will be taken to determine the P_c_CO_2_. We chose to take a capillary blood gas sample because there is a strong correlation between samples collected from the fingertip capillaries and the arterial blood samples in relation to the analysis of blood [26].

These measurements determine the safety for participants to start the first phase of the study. The start of the first phase of the study will be determined as safe if the participant is stable enough to undergo surgery (defined by neurosurgeon), capillary blood gas shows a P_c_CO_2_ between 4.5 and 6.5 kPa, and there are no symptoms of SAS or, in the case of SAS, the participant is adequately set to SAS treatment with an Apnea-Hypopnea Index (AHI) <5. These cut-off values have been chosen according to the applicable guidelines in the Netherlands [27].

#### ITB Trial (Phase 1)

Before definitive treatment with ITB, individuals will undergo an ITB trial by continuous infusion using an extracorporeal pump. We opted for this type of trial treatment based on a study by Bensmail et al [3], which demonstrated that a bolus infusion mode gave relatively more increase in the respiratory disturbance index and of central and mixed sleep apneas than the continuous infusion mode.

During phase 1, participants will be admitted to MST in Enschede. A hybrid infusion system consisting of a spinal catheter (Medtronic Ascenda 8781; Conformité Européenne [CE] mark for intrathecal use) and an implantable infusion port (Cellsite spinal; CE mark for intrathecal use) will be implanted under deep sedation. The participant lies in a lateral decubitus position. After marking the incision locations in the midlumbar region and the paraumbilical area, the incision areas will be infiltrated with local anesthesia (bupivacaine). After sterile draping, the lumbar fascia is exposed through a 2- to 3-cm incision, and a 16 T-gauge introducer needle will be placed to access the intrathecal space. Then, the spinal catheter will be placed under fluoroscopic guidance to the cervical level just below the level of injury. Once positioned, an anchor will be placed over the catheter and sutured to the deep fascia of the musculus erector spinae. The catheter will then be tunneled subcutaneously from the midlumbar region to the paraumbilical area and will be connected to the subcutaneous infusion port. Before wound closure, the port will be accessed to document the cerebrospinal fluid flow through the complete hybrid system. Thereafter, an extracorporeal pump (CADD solis infusion pump, CE mark for intrathecal use or application) will be connected percutaneously to the subcutaneous infusion port.

For safety reasons, we chose to start with the lowest possible dose given the concentration of baclofen and the infusion rate of the extracorporeal pump used. The starting dose of the ITB will be 1 µg per hour and is titrated in the following days based on both objective and subjective (participant’s experience) change in spasticity. In the literature, no maximum dose of ITB during a trial with an extracorporeal pump is reported. We set the maximum dose at 200 µg per day, based on our extensive previous experiences with the use of an extracorporeal pump in ITB trials.

Daily capillary blood gas samples will be taken, and continuous pulse oximetry during sleep, by use of the OSAsense, will be recorded. If the participant is set on a continuous positive airway pressure (CPAP) device, the CPAP device is read out. The trial will be determined as unsafe and will be stopped if the P_c_CO_2_ is >6.5 kPa for 2 days in a row, according to hypoventilation rules in adults as mentioned by Berry et al [28]. The trial will also be stopped when participants without SAS, during the trial, will develop complaints matching SAS and the Oxygen Desaturation Index (ODI) is between 5 and 15 [27]. The ODI represents the number of desaturations per hour.

A third reason to stop the trial is when participants during the trial have no complaints matching SAS, but the ODI is >15 [27]. If the participant uses a CPAP device, the setting of the device may be adjusted to stay within the safety margin. This safety margin is set at an AHI <5 [24]. This adjustment will be registered. A fourth reason to stop the study is when, after adjustments of the CPAP device, it is not possible to stay within this safety margin [24]. A fifth reason to stop the study is if there is no effect on spasticity at the maximum dose of ITB (200 µg per day).

If the participant experiences a positive effect of the ITB on their spasticity, with a score between 1 and 3 on the Patient Global Impression of Change (PGIC) [29] without deterioration on functionality (PGIC 5-7) and there is not a clinically relevant deterioration of pulmonary function or SAS, it is considered a safe and positive ITB trial with an indication for intracorporeal pump implantation (phase 2) and treatment with ITB at cervical level. We opted for these cut-off values for assessment of reduction of spasticity according to the algorithm established by the European working group for spasticity in adults [30].

If, during the trial, no effect is observed on spasticity or there is a clinically relevant deterioration of pulmonary function or SAS, the trial will be discontinued. This is considered a negative test in which there is no indication for treatment of spasticity with ITB. The catheter and the subcutaneous infusion port will then be removed (Figure 2)*.*

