#### Primary Outcome Measures

The primary objective of the study is to establish whether cervical administration of ITB is a safe treatment for spasticity without deterioration of pulmonary function and possible increased risk or increased severity of SAS. Safety will be determined by use of a capillary blood gas sample and an OSAsense or CPAP screening before and during the first phase of the study. We will use P_c_CO_2_ and the AHI or ODI as safety markers.

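### In CPAP users, device adjustment during infusion can hold the primary sleep marker below its limit, and no stated rule counts that adjustment as a sleep event

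*Protocol article*

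**What the plan says.** All references are to the Protocol article.

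- **Objective and marker.** Primary Outcome Measures asks whether treatment is safe, including whether SAS becomes more likely or more severe. It then states: "We will use P_c_CO_2_ and the AHI or ODI as safety markers". The information comes from an OSAsense or CPAP screening before and during phase 1. Secondary Outcome Measures adds that in CPAP users the AHI is taken from the device's own data.
- **Entry.** Screening and Recruitment admits people with SAS once treatment holds AHI below 5. Where screening raises suspicion, "polysomnography will be performed, and the patient will be set up for SAS treatment if necessary".
- **During infusion, CPAP users.** ITB Trial (Phase 1): "If the participant uses a CPAP device, the setting of the device may be adjusted to stay within the safety margin". The margin is AHI below 5. The next relevant sentence reads: "This adjustment will be registered". The fourth stopping reason is that "after adjustments of the CPAP device, it is not possible to stay within this safety margin".
- **During infusion, ODI rules.** Participants without SAS stop if they "develop complaints matching SAS and the Oxygen Desaturation Index (ODI) is between 5 and 15". A further reason to stop is when "participants during the trial have no complaints matching SAS, but the ODI is >15".
- **Verdict on the trial phase.** The same section calls a trial safe if, among other things, lung function and SAS have not worsened to a clinically relevant degree. It does not say how a CPAP adjustment bears on this.
- **Analysis.** Statistical Analysis plans descriptive pre/post comparison, cross tabs and visual exploration of individual change, without formal testing.

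**The concern.** The marker that is meant to reveal worsening sleep apnea is, in CPAP users, controlled by a co-intervention that responds to that same marker. A participant whose AHI rises on ITB and is brought back by a new device setting begins below 5 and ends below 5. The need for a changed setting is itself evidence that SAS became harder to control, which is what the primary objective asks about. Yet the stated markers are PcCO2 and AHI or ODI, and the adjustment is not among them.

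The Introduction gives muscle weakness and central dampening as reasons why cervical ITB might worsen sleep apnea. Participants already treated for SAS are therefore a group in whom the safety question matters, and with 11 participants a few uncounted events would change the reported picture.

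**Working it through.** **1. Figure to reproduce.** There is none. Sample Size says that no calculation was done and that 11 was taken from a comparable earlier study. Phase 1 has no test, margin or power statement. The check is of how the stated rules act together, followed by an illustration of size.

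**2. The stated rules side by side.**

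| | CPAP user | Participant without CPAP |
|---|---|---|
| Condition at entry | treated AHI <5 | no symptoms of SAS |
| Marker in phase 1 | device AHI | ODI from oximetry |
| Response to a worse value | setting may be adjusted and is registered | no corresponding adjustment described |
| Sleep stop rule | AHI <5 not achievable after adjustment | ODI 5–15 with complaints, or ODI >15 without |

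Consider a CPAP user whose AHI rises above 5 on ITB and falls below 5 after adjustment. The entry condition was met, the margin is met again, and the fourth stopping reason is not triggered. No stated rule then turns the episode into an outcome event.

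**3. Baseline.** Table 1 marks pulse oximetry at T0A1 and T0B but not at T0A2, so the only tabulated sleep measurement before infusion is at screening. For someone who starts SAS treatment because of that screening, the tabulated value can predate treatment. Primary Outcome Measures does allow a CPAP screening before phase 1, so an on-treatment baseline is available. The article does not say which of the two is compared.

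**4. Illustration of size.** Let k be the number of CPAP users among n = 11. k is not in the document and is assumed. Take the limiting case in which all their worsening is correctable and uncounted, so that 11 − k participants can show a sleep event.

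- One-sided 95% upper bound with zero events: 1 − 0.05^(1/(11 − k)).
- Chance that nobody is flagged at true worsening risk p: (1 − p)^(11 − k).
- Expected observed share: p(11 − k)/11.

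| k | 11 − k | Upper bound, 0 events | None flagged, p = 0.20 | None flagged, p = 0.30 | Expected share, p = 0.20 |
|---|---|---|---|---|---|
| 0 | 11 | 23.8% | 8.6% | 2.0% | 20.0% |
| 2 | 9 | 28.3% | 13.4% | 4.0% | 16.4% |
| 4 | 7 | 34.8% | 21.0% | 8.2% | 12.7% |
| 6 | 5 | 45.1% | 32.8% | 16.8% | 9.1% |

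For example, at k = 4: 1 − 0.05^(1/7) = 0.348, and 0.8^7 = 0.210. Both values of p are assumptions.

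**5. Effect of counting adjustments.** With exact two-sided 95% intervals, 0/11 (0 to 28.5%) would become:

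- 1/11 = 9.1% (0.2 to 41.3%) with one adjusted CPAP user;
- 2/11 = 18.2% (2.3 to 51.8%) with two;
- 3/11 = 27.3% (6.0 to 61.0%) with three.

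These counts are assumed.

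**The case against.** The strongest reply is that the article is silent rather than wrong. Adjustments are registered, the device is read out, and an adjustment made to stay within the margin presupposes an observed rise, so the worsening is traceable. Worsening that CPAP cannot correct is caught by the fourth stopping reason. Daily PcCO2 with its own stop rule covers everyone. Oximetry during sleep is described for phase 1 without exempting CPAP users, and the ODI >15 rule is not worded as limited to people without SAS, so ODI may exist for CPAP users as well. How a registered event is counted could be left to a fuller document.

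Much of this stands, and it rules out several stronger readings that a reader might infer:

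- *That worsening in CPAP users is recorded as an absence of deterioration.* No sentence says so.
- *That CPAP users cannot show worsening unless CPAP fails completely.* The rise before adjustment should be in the device data, and the stop rule needs only that AHI <5 cannot be kept.
- *That AHI and ODI are pooled.* This is not stated, and exploring change within each participant does not require it.
- *That starting CPAP will look like a benefit of ITB.* This would need untreated screening oximetry as the comparator, which the article does not specify.

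What does not fall away is the core. The article itself fixes the markers, the margin, the adjustment rule and the stopping reasons, and together they let a correctable worsening through. Registration makes the event recoverable but does not make it an outcome. PcCO2 measures hypoventilation rather than apnea severity, and any oximetry on CPAP would be affected by the same adjustment.

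A further fair objection is that counting every adjustment would give deterioration a second meaning, beside the one that ends the trial phase, and could include changes made for other reasons. This should shape the fix.

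**Conclusion.** The concern holds in a limited form. Under the stated rules, an ITB-related worsening of SAS that CPAP can correct can pass as safe, because the primary marker in CPAP users is held below 5 by adjustment and the registered adjustment has no stated place in the primary safety outcome.

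The size depends on the number of CPAP users, which the document does not give. In the limiting case, zero observed events would carry an upper bound of 28.3% (k = 2) or 34.8% (k = 4) instead of 23.8%. That bound would describe only participants without CPAP. If some worsening in CPAP users is not correctable, or is reported from the register, the loss is smaller. The documents do not support a claim of demonstrated bias in the baseline or of pooled indices; on both, a clarifying statement is enough.

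**What to change.** Change the analysis only, leaving CPAP management and all stopping rules as they are.

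1. In the primary safety summary, count any CPAP adjustment made after infusion starts to restore AHI below 5 as a sleep-worsening event. Report it under its own label, separate from the criterion that ends the trial phase, and leave out adjustments made for other reasons.
2. Report the device AHI before the adjustment as that participant's worst value.
3. State that the baseline for CPAP users is the on-treatment AHI required for entry, which Primary Outcome Measures already allows, and not the T0A1 oximetry.
4. Tabulate AHI (CPAP users) and ODI (others) separately, and give the number of CPAP users.

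The cost is mainly wording, since adjustments are registered and device data are read out; the register must show why each adjustment was made. The downside is that more participants will be counted with sleep worsening. The change is best made now: Results reports six participants enrolled in phase 1 and no analysis done, and Study Coordination has the safety board review the study once the first six have completed phase 1.

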**Figure 2 figure2:**
[figure not shown]
Overview of phase 1. CPAP: continuous positive airway pressure; PGIC: Patient Global Impression of Change.

#### Baclofen Pump Implantation (Phase 2)

In the case of a positive ITB trial phase, the infusion port will be replaced by a definitive pump system. In this procedure, the participant is in a supine position and under deep sedation or local anesthesia. The infusion port is removed from the catheter, and the catheter is connected to a programmable implantable pump (Medtronic SynchroMed II; CE mark) for intrathecal drug delivery.

One day after the pump implantation at the MST, participants will be transferred to RCR. Participants will remain in the rehabilitation center for at least 2 weeks. During admission, the dosage of ITB will be slowly increased, and the oral spasmolytics will be phased out. Spasticity is measured on a daily basis, and for safety reasons, once a week and at discharge, a capillary blood gas sample is taken and a screening with the OSAsense is performed, or CPAP data are checked. The participant will be discharged home when the oral spasmolytics are phased out, the patient is satisfied with the current level of spasticity (PGIC between 1 and 3), and the AHI or ODI and P_c_CO_2_ are within the safety margins, as indicated previously. The participant will be seen for follow-up at the rehabilitation center at 3, 6, and 12 months after implantation. To promote follow-up, the participants will be called once before their appointment by the primary investigator. In case a participant stops or deviates from the protocol, the reason for this will be recorded.

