## Methods

### Study Design

This multiphase single-arm intervention study will contain 2 phases. We will first start with screening and recruitment to determine if there is an indication for, and if it is safe to start treatment with ITB. Phase 1 will be the safety phase, in which an extracorporeal pump will be used to investigate whether cervically administered ITB leads to reduction of spasticity without adverse effect on pulmonary function and sleep-related disorders. In case of a safe and positive test, we will continue to the next phase (phase 2) in which a baclofen pump is implanted. After implantation, the dosage of ITB will be slowly increased to the optimal setting, and if the participant uses oral spasmolytics, these are phased out. The optimal setting varies in accordance with patient conditions. In this phase of the study, we will focus, in addition to pulmonary function and sleep-related disorders, on the reduction of spasticity; improvement of participants’ level of function, activities, and participation; and participant satisfaction according to the International Classification of Functioning [11].

All participants will be assessed once before the start of phase 1 (T0A1), at the start of phase 1 (T0A2), and daily during phase 1 (T0B). In the case of a safe and positive test, participants will be assessed at the end of phase 1 (T1). During phase 2, they will be assessed at 3, 6, and 12 months (T2, T3, and T4) after baclofen pump implantation. We chose to start the assessment in phase 2 only after 3 months following the implantation because in the first 3 months, the pump settings will still be regularly adjusted to optimize the daily dosage of ITB.

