**Participants and disease characteristics**																				
	Sex	✓																		
	Race	✓																		
	Age	✓																		
	Level and completeness of the SCI^r^	✓															International Standards for Neurological Classification of Spinal Cord Injury			
	Etiology of SCI	✓																		
	Time since injury	✓																		
	Other treatments against spasticity	✓																		
	Medication	✓		✓		✓		✓		✓			✓		✓					
	Comorbidity	✓		✓		✓		✓		✓			✓		✓					
	Vital signs	✓		✓		✓		✓												
	Complications and side effects			✓		✓		✓		✓			✓		✓					

^a^T0A1: preassessment screening.

^b^T0A2: start of the extracorporeal pump.

^c^T0B: period during the trial phase.

^d^T1: moment appropriate titration in the trial phase.

^e^T2: 3 months after implantation.

^f^T3: 6 months after implantation.

^g^T4: 1 year after implantation.

^h^If there is any suspicion of sleep apnea syndrome based on the results of the pulse oximetry, additional polysomnography will be performed during the screening and recruitment.

^i^If participants during the trial phase experience dyspnea, spirometry will be performed.

^j^PGIC: Patient Global Impression of Change.

^k^PRPM: Perceived Resistance to Passive Movement.

^l^MAS: Modified Ashworth Scale.

^m^MRC: Medical Research Council.

^n^ROM: range of motion.

^o^COPM: The Canadian Occupational Performance Measure.

^p^GRT: Grasp and Release Test.

^q^QIF-sf: Quadriplegia Index of Function—Short Form.

^r^SCI: spinal cord injury.

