#### Secondary Outcome Measures

The secondary objective of the study is to explore the effect of cervical administration of ITB on the reduction of spasticity; intermediate and long-term effects on pulmonary function and SAS; and improvement in the level of participants’ function, activities, and participation [11]. Participant satisfaction will also be considered.

All secondary outcome measures are carried out in RCR at screening and at 3, 6, and 12 months after implantation of the baclofen pump by an experienced and trained physiotherapist and occupational therapist. Spasticity and satisfaction will also be measured during phase 1.

Spasticity is measured by the MAS [19] and PRPM [20]. Spasticity will be measured in the UE and LE. The PRPM is an ordinal scale that measures and describes perceived resistance against passive motion. The scale ranges from 0 (no increase in resistance) to 4 (limb is rigid in flexion or extension). During testing, the patient is in a relaxed position (the position of the patient is documented). The patient is instructed not to assist or oppose the movement. First, the passive range of motion of the joint is tested by slow flexion or extension. Subsequently, perceived resistance is assessed within the entire range with a faster movement, covering the whole range within 1 second. The movement can be repeated a maximum of 2 times (the lowest score is noted).

The MAS measures the increase in muscle tone and assigns a grade of spasticity from a 0 to 4 ordinal scale. A score of 0 signifies normal muscle tone, a score of 1 signifies a slight increase in muscle tone with a slight catch when the limb is moved in flexion and extension, a score of 1^+^ signifies a slight increase in muscle tone with minimal resistance at the end of movement, a score of 2 signifies a more marked increase in muscle tone through the entire movement but the limb is still easy to move, a score of 3 indicates a considerable increase in muscle tone and that passive movement is difficult, and a score of 4 indicates that the limb is rigid in flexion or extension. The position of the patient and the procedure is the same as in the PRPM.

Participant satisfaction will be measured by PGIC [29], which is a 7-point scale ranging from 1 (very much improved) to 7 (very much worse). Using the scale, the participant can rate if the ITB has changed the level and the hindrance of the spasticity according to the situation before cervical administration of ITB.

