### Statistical Analysis

Because of the small sample size, it is expected that the continuous variables will not be parametrically distributed; therefore, they will be presented as median with IQR. Furthermore, due to the small sample size, pre- and postassessments during the first phase or the ITB trial phase will be compared with descriptive statistics and differences will not be formally tested. In addition, the measurements in the second phase after definitive implantation of the baclofen pump (3, 6, and 12 months after implantation) will be compared with descriptive statistics. Changes over time in the outcome measures within patients will be visually explored.

For categorical variables, we will present numbers and corresponding percentages. To compare pre- and postassessment during the first phase or the ITB trial, cross tabs will be made. Our primary analysis population is the intention-to-treat analysis. Considering the study design, we expect a few missing data. In case of missing data, we will use generalized estimation equations analysis (<20% missing data) or multiple imputations (>20% missing data).

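### Respiratory and sleep checks taken while the dose is raised after implantation have no time point and no stated analysis, so a transient breach of the safety margins there would be missing from the safety results

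*Protocol article*

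**What the plan says.** The Protocol article fixes four things that bear on this.

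- **Measurement.** Under Baclofen Pump Implantation (Phase 2), participants stay at the rehabilitation center for at least 2 weeks. In that stay "During admission, the dosage of ITB will be slowly increased" and oral antispastic drugs are withdrawn. For safety, "once a week and at discharge, a capillary blood gas sample is taken and a screening with the OSAsense is performed"; the alternative is a check of CPAP data. Discharge requires, among other things, that AHI or ODI and PcCO2 lie within the margins given earlier.
- **Safety determination.** Under Primary Outcome Measures: "Safety will be determined by use of a capillary blood gas sample and an OSAsense or CPAP screening before and during the first phase", with PcCO2 and AHI or ODI as the markers.
- **Schedule.** Under Study Design: "We chose to start the assessment in phase 2 only after 3 months following the implantation". The reason given is that "in the first 3 months, the pump settings will still be regularly adjusted". In Table 1 the column after T1 (end of the ITB trial) is "T2: 3 months after implantation". Under Secondary Outcome Measures, which include intermediate and long-term respiratory and sleep apnea effects, measurements are "carried out in RCR at screening and at 3, 6, and 12 months after implantation of the baclofen pump"; only spasticity and satisfaction are added, in phase 1.
- **Analysis.** Under Statistical Analysis, phase 1 is described before against after, and "the measurements in the second phase after definitive implantation of the baclofen pump (3, 6, and 12 months after implantation) will be compared" descriptively.

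**The concern.** The objective is whether cervical ITB is a safe treatment. The Introduction's own argument for possible harm is that higher cervical concentrations may weaken respiratory muscles and worsen sleep apnea. A period of rising dose is therefore directly relevant, and the protocol measures the right markers in it. As written, those values serve only the individual's care and discharge.

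The discharge condition makes the gap selective. A participant discharged under the protocol must be back within the margins, so a breach during the admission has by then been corrected. It may leave no trace at 3 months, when the pump has been adjusted for weeks. The safety results could then show no breach in a participant who had one on the trial's own markers.

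**Working it through.** The point is structural. The article states no sample size calculation, alpha or trial-level safety threshold, so there is no figure of the plan to reproduce.

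**Step 1: does any stated element reach the admission values?**

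| Element of the article | Period covered | Reaches the post-implantation admission? |
|---|---|---|
| Primary Outcome Measures | Before and during phase 1 | No |
| Table 1 | Screening, T0A2, T0B, T1, then 3, 6, 12 months | No |
| Secondary Outcome Measures | Screening, 3, 6, 12 months (spasticity and satisfaction also in phase 1) | No |
| Statistical Analysis, named comparisons | Phase 1 before/after; 3, 6, 12 months | No |
| Discharge condition | End of admission | Yes, for individual care only |
| Complications, side effects, serious adverse events | During the study | Yes, but as events, not as marker values |

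Table 1 lists blood gas, oximetry and spirometry at T2 to T4 under primary outcomes, which sits uneasily with the phase 1 wording under Primary Outcome Measures. Even on the wider Table 1 reading, nothing lies between T1 and 3 months.

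**Step 2: how many measurements are involved?** A 2-week stay with weekly sampling plus discharge gives 2 checks if the second weekly one coincides with discharge, otherwise 3. If all 11 participants were implanted (an assumption; the number will depend on phase 1), that is 11 × 2 = 22 to 11 × 3 = 33 blood gases, and as many sleep checks, at the minimum stay. For the 3 participants reported in phase 2 in June 2025 it is 3 × 2 = 6 to 3 × 3 = 9.

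**Step 3: what could one uncounted breach change? (illustration only)** With 0 of n, the exact one-sided 95% upper bound is 1 − 0.05^(1/n). With 1 of n, it is the p that solves (1 − p)^n + n·p·(1 − p)^(n−1) = 0.05.

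| n implanted (assumed) | 0 breaches: rate, upper bound | 1 breach: rate, upper bound |
|---|---|---|
| 11 | 0%, 23.8% | 1/11 = 9.1%, 36.4% |
| 6 | 0%, 39.3% | 1/6 = 16.7%, 58.2% |

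**Step 4: how likely is at least one breach?** The documents give no rate. Over an assumed range of risk p per participant, the chance is 1 − (1 − p)^n.

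| Assumed p | n = 3 | n = 6 | n = 11 |
|---|---|---|---|
| 5% | 14% | 27% | 43% |
| 10% | 27% | 47% | 69% |
| 20% | 49% | 74% | 91% |

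**Step 5: direction.** Adding the admission values to a count of participants with any breach, or to a worst value per participant, can leave the result unchanged or make it less favourable. It cannot make it more favourable.

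**The case against.** The strongest reply has four parts.

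1. **Harm is captured elsewhere.** Complications, side effects, serious adverse events and suspected unexpected serious adverse reactions are registered, reasons for stopping or deviating are recorded, and a data safety monitoring board is involved throughout. This stands. A reader might infer that harm during escalation is ignored altogether; the documents do not support that. But the board's one named review follows phase 1 in the first 6 participants, and an asymptomatic, corrected PcCO2 or ODI breach need not be entered as an event.
2. **The analysis text is not closed.** It also says that within-patient changes over time in the outcome measures will be explored visually, without restricting the visits. This leaves some room. However, Table 1 sets the timing of the outcome measures, Study Design starts phase 2 assessment at 3 months, and the named comparisons list the visits.
3. **It is a deliberate choice, and monitoring values need not be endpoints.** Waiting for stable settings is a sound reason for timing efficacy measures late. It is a weaker reason for setting aside safety markers, since the unstable period is where a safety signal may arise.
4. **Details may sit in a full protocol or analysis plan that is not shown.** The layout of listings may. The safety window, time points and compared visits are stated in the article itself, and together they leave the admission out.

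**Conclusion.** The point holds in limited form. The weekly and discharge PcCO2 and ODI or AHI values are collected for safety but have no time point, outcome or named analysis. The loss is confined to a transient or corrected breach during the admission; a lasting change could still appear at 3 months. It is worth correcting before analysis, and it does not undermine the phase 1 safety assessment.

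Two further inferences should be resisted. One is that phase 1 is judged at doses far below those of phase 2: the article gives a phase 1 starting dose and cap but no phase 2 dose, so that gap cannot be sized. The other is that the safety conclusion is shown to be biased. The direction of the omission is clear, but whether any breach will occur is unknown, and the percentages above rest on assumed rates and numbers implanted.

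**What to change.** - Add a phase 2 titration time point to Table 1 (post-implantation admission, weekly and at discharge) for PcCO2 and ODI or AHI, and assign it to the safety outcome.
- Report descriptively, per participant, the worst value during the admission and whether any safety margin already stated in the protocol was crossed, next to the ITB dose running at that time. The phase 1 PcCO2 stopping criterion concerns 2 days in a row, which weekly samples cannot show, so the report should say how a single value is classified. This is for description only and changes no clinical rule.
- State that no scheduled sampling is described between discharge and 3 months, so the safety conclusion does not cover that interval. The change recovers the admission period only.

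**Cost.** One column in Table 1 and a few lines of analysis text; the measurements are already taken. The article does not say where the dose at each check is recorded, so the case report form may need a field for it, and values may have to be retrieved for participants already implanted. The article reports that no data analysis had been done, so the change can still precede the results. The downside is slightly more descriptive work and a safety result that may look less favourable.
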